## Abstract

**Background:**

Cancer survival is lower in socioeconomically deprived communities, partly due to low awareness of symptoms, negative beliefs and delayed help-seeking. We developed an interactive health check questionnaire facilitated by trained lay advisors. It entails 29 questions about background, lifestyle and health with tailored behaviour change advice. Personalised results are printed using a traffic light (red/amber/green) system, highlighting areas where action should be taken. This is an individually randomised control trial to test effectiveness of the health check on symptom recognition.

**Methods:**

A total 246 participants aged 40+ years will be recruited from community and healthcare settings in socioeconomically deprived areas of Yorkshire and South Wales. Participants will be randomised to receive the health check or standard care (1:1 ratio). Outcome measures include: adapted Awareness and Beliefs about Cancer (primary outcome), brief State Trait Anxiety Inventory, intentions and motivation to adopt recommended health behaviours (early symptom presentation, cancer screening and lifestyle behaviours), adapted Client Service Receipt Inventory, brief medical history/screening and demographic questionnaire at: baseline; 2-weeks; and 6-months post-randomisation. A purposive sample of intervention sessions will be audio-recorded (*n* = 24) and half will additionally be observed (*n* = 12). Semi-structured interviews will take place at 2-weeks (*n* = 30) and 6-months (*n* = 15–20) post-randomisation. The primary analysis will compare cancer symptom recognition scores between arms at 2-weeks. Secondary analysis will assess cancer beliefs, barriers/time to presentation, screening and lifestyle behaviours, anxiety and costs. A process evaluation will assess intervention fidelity, dose and contamination.

The London-Surrey NHS Research Ethics Committee (Ref: 17/LO/1507) approved this trial.

**Discussion:**

This is a trial of a theoretically underpinned complex intervention which has undergone phase 1 and 2 development work. The findings will evaluate evidence about the effect of the health check on symptom awareness. Although there are few exclusion criteria there are limitations regarding the population we are able to reach, who may have even higher risks of late diagnosis and poor cancer prognosis. However, the health check has the potential to improve cancer symptom awareness and encourage early help-seeking behaviour in deprived populations, thereby reducing inequalities in longer term cancer outcomes.

**Trial Registration:**

Retrospectively registered with ISRCTN (Ref:ISRCTN16872545) on 12.01.2018.

## Background

Cancer outcomes are considerably poorer in the most socioeconomically deprived areas of the UK [1–3], including West and South Yorkshire and South Wales. This reflects high risk lifestyle behaviours (e.g. smoking, poor diet, low exercise) which have been linked to increased risk of developing cancer [4]. Evidence suggests that low awareness of cancer symptoms, fear of cancer or fatalistic beliefs about cancer and concerns over wasting the doctor’s time are higher in lower socioeconomic groups [5] resulting in delayed help seeking [5–8], in turn leading to late stage diagnosis and lower uptake of cancer screening [9]. There is a need for interventions which overcome this, by addressing negative beliefs about cancer and highlighting the benefits of early diagnosis, as well as raising awareness of potential cancer symptoms, in order to reduce the time to symptom presentation and improve long term treatment outcomes.

Mass media awareness campaigns have been widely used across public health with the aim of changing a range of health behaviours (including increasing cancer knowledge and symptom recognition and encouraging help seeking behaviour) [10]. Emerging evidence suggests that targeted, intensive community-based behaviour change interventions may be more successful at improving cancer awareness in high risk disadvantaged populations [11–15]. In particular, interventions that draw on pre-existing social networks and social influences [16] have the potential for more successful outcomes in this context. Involving trusted and trained lay advisors may be a successful method for engaging and delivering cancer messages in a compassionate and non-judgmental manner to people living in deprived communities [11, 17]. However, the Improving Rural Cancer Outcomes (IRCO) trial of a community-based symptom awareness and GP educational intervention in rural Western Australia did not observe a significant effect of the intervention on time to symptom presentation [18]. The authors suggest that this may reflect limited intervention “dose”. It is therefore important to consider the optimal dose and intensity of cancer awareness interventions targeted at high risk disadvantaged populations.

While previous targeted community-based complex interventions that use evidence-based behaviour change techniques (BCTs) are promising in encouraging cancer awareness and earlier help-seeking [12–14], high quality evidence is needed to test intervention effectiveness in ‘real life’ settings. The ABACus 3 trial is testing a tailored health check intervention facilitated by a lay advisor in deprived communities in South and West Yorkshire and South Wales.

### Health Check intervention

We developed and piloted a community outreach health check intervention facilitated through a lay advisor, designed to improve cancer symptom knowledge, encourage positive beliefs in relation to early cancer detection, and increase motivation to seek help among adults living in deprived communities [16, 19]. The health check has been informed by a theoretical understanding of the barriers and enablers to timely help-seeking among people living in disadvantaged communities [19–21], and comprises an interactive touchscreen questionnaire with behavioural support delivered face-to-face by a trained lay advisor (see Fig. 1 for screenshot of the touch screen questionnaire). The intervention is primarily designed to reduce the “patient interval”, defined as the time between appraising a bodily change as a potential symptom of cancer and presenting in primary care [7]. It also attempts to integrate early symptom detection with cancer screening and cancer prevention recommendations, by including content relating to cancer symptoms, screening, and risk factors (i.e. smoking, diet and inactivity).

**Fig. 1 Fig1:**
[figure not shown]
Screen shot of the ABACus Health check ‘Your Health’ Section

In line with the Medical Research Council guidance on developing and evaluating complex interventions [22], two phases of development and feasibility/pilot testing were undertaken in partnership with local stakeholder groups. Findings from phase 1 suggested that the health check is beneficial and acceptable to members of the public, health professionals and community partners living and working in deprived areas of South Wales [19]. Results from phase 2 demonstrated the feasibility and acceptability of recruiting people from healthcare and community settings within disadvantaged communities to undertake the health check [16].

The health check comprises 29 questions divided into three main sections; *‘About You’*, *‘Your Lifestyle’* and *‘Your Health’*. Questions are tailored according to participants’ age and gender (See Table 1 for a breakdown of the questions). Individualised results are provided in a ‘*Results*’ section and are displayed using a traffic light system, with ‘green’ indicating results where no signposting or change is suggested, ‘amber’ indicating an area where signposting or change could be considered, and ‘red’ results indicating that action should be taken. Information and signposting to relevant services (for example, stop smoking and weight loss services) are provided by the lay advisors, based on individual results and tailored to local availability. The intervention manual details all written and verbal information to be provided to participants for each response type across each question. It also maps out each of the BCTs to be used within each section. Lay advisors are extensively trained to deliver the intervention and are formally assessed to ensure familiarity with all components of the intention (i.e. ‘About You’, ‘Lifestyle’, ‘Your Health’) and associated BCTs tailored according to individual responses.

**Table 1 Tab1:** Interactive Health Check Questions

Sections	Questions
Section 1: About You	Have you ever been diagnosed with cancer?
	Do you have 2 or more close relatives who have been under the age of 50 when diagnosed with cancer?
	Please give your height in Feet and Inches / Centimetres Please give your weight in Stones and Pounds/Kilos
	Did you receive your bowel screening kit in the post? If yes, did you send it back?
	Have you been invited for a cervical smear test? If yes, did you attend?
	Have you been invited for your breast screening test? If yes, did you attend?
Section 2: Your Lifestyle	Do you smoke? If yes, On average How many cigarettes a day do you smoke
	Are you exposed to another person’s smoke on a regular basis?
	Do you drink alcohol? If yes, on average How many units of Alcohol do you drink each week?
	On average, how many hours a week do you exercise in total, adding up any daily amounts?
	How often do you eat 5 portions of fruit and vegetables in a day?
Section 3: Your Health	Do you have a cough that won’t go away? If yes, do you bring up blood when you cough?
	Have you noticed any unusual lumps on your body (e.g. breasts, testicles, armpits, groin)?
	Have you noticed a change in how your skin looks (e.g. change to a mole, freckle or patch of skin)?
	Do you have a sore or ulcer in your mouth that will not heal?
	Have you noticed a change or any blood in your poo?
	Do you have any problems when peeing?
	Do you have any unexplained bleeding (e.g. blood in your pee, bleeding from your bottom, vaginal bleeding during /after sex or in between periods)?
	Do you have difficulty swallowing?
	Have you been losing weight without trying to?
	Have you noticed any unexplained change in your appetite?
	Do you feel tired most of the time?
	Do you have an unexplained pain that won’t go away?

### Aim and Objectives

The aim of the trial is to evaluate the effectiveness of a community-based cancer awareness intervention in socioeconomically deprived communities. Specific objectives are to:Test the effects of the health check on cancer symptom awareness and help-seeking behaviour among adults living in socioeconomically deprived communities in South and West Yorkshire and South-East Wales.Evaluate the costs associated with the health check and estimate the cost-effectiveness of the intervention.Assess whether the intervention was delivered as intended, whether there are any contaminating factors to understand the mechanisms of change.

## Methods

### Patient and Public Involvement

The trial team includes two patient/public research partners (one of whom was also involved in the phase 2 study) who provide support and knowledge at every stage of the research process. One partner lives in one of the target recruitment areas, the other has significant family associations with the other area. Both have been affected by cancer.

The research partners have been critical for the early development and set-up of the trial and have provided detailed input to the protocol development. They additionally contribute to all public facing materials (i.e. information booklet content and design, questionnaire design etc.), generate ideas on how best to engage the target population, support data interpretation as well as provide ideas on dissemination opportunities.

### Trial design and setting

This is an unblinded individually Randomised Controlled Trial of an online Cancer Health Check intervention with additional tailored verbal information delivered by a lay advisor in areas of high deprivation in South and West Yorkshire (i.e. Sheffield, Wakefield, Barnsley, Doncaster, Rotherham etc.) and South-East Wales (i.e. Merthyr Tydfil, Newport etc.) UK. See Fig. 2 for a flow diagram of the trial design.

**Fig. 2 Fig2:**
[figure not shown]
Trial Flow diagram

Areas of high deprivation are identified using the Index of Multiple Deprivation (IMD) for England [23] and the Welsh Index of Multiple Deprivation (WIMD) for Wales [24]. Settings include community (local community groups, one-to-one community sessions, community events) and healthcare (GP practices and community pharmacies) venues.

This protocol has been drafted in accordance with the SPIRIT guidelines [25].

### Participant selection

All participants must meet the following eligibility criteria.

Inclusion criteria:Aged 40 years and over.Recruited from socioeconomically deprived areas (i.e. lowest quintile) of South and West Yorkshire (i.e. Sheffield, Barnsley, Rotherham, Wakefield) as measured by the IMD [23] or South-East Wales (i.e. Merthyr Tydfil and Newport) as measured by the WIMD [24].

Exclusion criteria:Non-English speakers.Unable to give written informed consent (as defined by Good Clinical Practice [26]).A participant from the phase 2 study.

### Outcomes

The primary outcome is cancer symptom knowledge [27] including specific (e.g. rectal bleeding, unusual lump) and non-specific (e.g. tiredness, unexplained weight loss) symptoms measured at two weeks post-randomisation.

Secondary outcomes include: cancer beliefs [27]; barriers to presentation [27, 28]; help-seeking intentions [27]; state anxiety [29]; intervention implementation costs; cost-effectiveness; intentions and confidence to adopt recommended health behaviours where relevant (smoking, physical activity, weight loss, fruit and vegetable intake, alcohol consumption, screening attendance, symptom presentation) [4, 30].

### Measures

The following measures will be used:Adapted Awareness and Beliefs About Cancer questionnaire (ABC) [27].(The ABC measure was adapted to be used with this population during phase 2 and has been further refined following phase 2 findings. Changes made mainly focus on phrasing and wording of questions to ensure they are clearly understood by the target population.)Six-item short-form State-Trait Anxiety Inventory (STAI-6) [29].Client Service Receipt Inventory.Behavioural intentions and confidence questionnaire developed using Theory of Planned Behaviour [30].

### Participant Identification & Recruitment

Participants will be identified and recruited by the lay advisors with support from local site staff and/or local research nurses/officers where possible. Recruitment days will be arranged in advance and will take place at local facilities within communities identified as areas of high socioeconomic deprivation (using the IMD and WIMD).

A total of 246 participants will be recruited to the trial, with two thirds (*n* = 164) of participants recruited from South/West Yorkshire and one third (*n* = 82) recruited from South-East Wales over a 15 month period. This reflects strategic priorities of the funder to address the needs of the Yorkshire population, while recognising similarities in the sociodemographic characteristics of the populations across the two geographical sites.

Venues will provide access to a private room to ensure participant privacy and confidentiality. Two recruitment methods will be used: Route 1 - pre-booked appointments, and Route 2 – opportunistic. Wherever possible, pre-booked appointments (with support from local staff) will be used to book in interested individuals. Opportunistic recruitment will be used where local staff are unable to support the appointment system. In such instances, lay advisors will either visit venues a few days in advance to approach individuals and book them in for the upcoming recruitment day or approach potential recruits on the day or a combination of both.

### Screening, registration and consent

The lay advisors will initially check participant eligibility verbally when individuals show an interest in the study and if confirmed as eligible will then proceed to full recruitment. The study will be explained to individuals with the support of the participant information booklets. Those individuals who proceed to recruitment will be asked to provide written informed consent at which point their eligibility will be formally confirmed (using a checklist) by the lay advisor. We will additionally seek consent from participants at recruitment to take part in the qualitative aspects of the trial (if relevant) and to be contacted in the future should a related follow-on study take place.

### Randomisation

Participants will be individually randomised to either intervention (facilitated health check) or control (usual available care/support) in a 1:1 ratio. Randomisation will occur immediately following baseline data collection and participants will be informed by the lay advisor of their allocation. A computerised random number sequence will be generated to indicate group allocation. This will be facilitated through a bespoke database. Lay advisors will be blind to the randomisation sequence in order to minimise any selection bias during recruitment and data collection. Only the direct trial team will have access to this information for back-up randomisation purposes.

### Data collection

Table 2 provides a breakdown of data collection across time points. A data management plan will outline how all data will be collected, managed and stored. All data will be managed in strict confidence according to GDPR (EU 2016/679).

**Table 2 Tab2:** Enrolment/Assessments schedule [42]

Procedures/Time point	Set-up	Screening	Baseline	Intervention	Follow-up	
	- 1 month	B (over 12 months)			+ 2 weeks	+ 6 months
Recruitment						
Eligibility assessment		X				
Informed consent			X			
Contact details form			X			
Randomisation			X			
Data collection						
Demographic questionnaire			X			
Medical history questionnaire			X			
Adapted ABC measure			X		X	X
Cancer worry			X		X	X
Lifestyle questionnaire			X		X	X
Resource use			X			X
Intervention Delivery						
Lay advisor training	X					
Intervention delivery or control				X		
Process measures						
Interviews with HCAs	X				X	
Site summary logs		X				
Lay advisor timesheets		X	X	X		
Observation/Audio recording of Intervention delivery				X		
Participant Interviews (2–6 weeks)					X	
Participant exit interviews (post trial)						X

Participants will complete the adapted ABC questionnaire at baseline, 2 weeks and 6 months post-randomisation. Baseline data will be collected electronically via an IPad and entered directly onto the bespoke trial database. Follow-up data will primarily be collection on the phone and inputted directly on the database, however if participants cannot be contacted after four attempts, paper case report forms will be sent via the post.

To support the process evaluation, a purposive sample (based on setting type, age and gender) of participants will be interviewed at 2–6 weeks post intervention delivery (*n* = 30) and post-trial (*n* = 15–20). A purposive sample (based on setting type, age and gender) of health check sessions (20%, *n* = 24/123) will be audio-recorded and half of these (10%, *n* = 12/123) will be purposive sampled (based on setting type, age and gender) to be additionally observed. Lay advisors will be interviewed before beginning participant recruitment and at the end of recruitment (n = 3 + 3). Site summary logs will be completed for each recruitment day to record further process data.

### Incentives

As a thank you for their time, participants will be offered high street shopping vouchers to the value of £15. They will receive a £10 voucher after completing the baseline questionnaire and a £5 voucher after completing the 6-month questionnaire. A sample of participants will be offered a further £10 voucher for taking part in an interview.

### Process evaluation

In parallel to the trial, a process evaluation will be conducted following the MRC guidance [31] to assess: fidelity (whether the intervention has been delivered as intended and as a measure of quality assurance); dose (whether tailored BCTs were delivered according to participant self-reported behaviours during the health check); contamination (whether there were any external factors that may have influenced participant behaviour/responses); reach (whether the target population received the intervention); key mechanisms of change (which components of the intervention may have caused change i.e. mapped BCTs according to domain questions e.g. increased symptom recognition as a results of increased capacity (i.e. specific knowledge and BCTs: *information about health consequences*)). The evaluation will draw on a combination of qualitative (observations and interviews) and quantitative (recruitment numbers, resource use, manual adherence) data.

Fidelity of adherence to the intended intervention delivery and tailored BCTs dose delivery will be assessed in the process evaluation. A sample of sessions (20%, *n* = 24/123) will be audio-recorded and half of these (*n* = 12/123) will additionally be observed to ascertain the extent to which the intervention was delivered according to the manual and to assess the levels of exposure. A structured coding framework will be developed to support the assessment of fidelity and dose.

### Sample size

A sample of 246 participants is required in order to achieve 90% power to detect an effect size of 0.5 in the primary outcome of cancer symptom recognition, using a two-sided test and 5% significance threshold, and assuming 30% attrition at two weeks follow-up. An effect size of this magnitude equates to intervention participants recognising on average one extra cancer symptom during the follow-up period (SD = 2.2) [32].

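### The sample-size text equates an effect of 0.5 SD with one extra symptom, but at its own SD of 2.2 that effect is 1.1 symptoms; one symptom is 0.45 SD

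*Protocol article*

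**What the plan says.** The Sample size section of the protocol article states: "A sample of 246 participants is required in order to achieve 90% power to detect an effect size of 0.5". The conditions are "using a two-sided test and 5% significance threshold" and "assuming 30% attrition at two weeks follow-up". The next sentence puts the effect on the symptom scale: "An effect size of this magnitude equates to intervention participants recognising on average one extra cancer symptom during the follow-up period (SD = 2.2"), with a literature reference for support. Allocation is 1:1 (Randomisation section).

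The Main analyses section plans a complete-case linear model of the 2-week score with baseline symptom recognition as a covariate, and promises the effect both with and without baseline adjustment, each with a 95% confidence interval. The Sample size section mentions no baseline adjustment and gives no correlation between baseline and follow-up.

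**The concern.** Three figures stand side by side: an effect size of 0.5, a difference of one symptom and an SD of 2.2. Any two of them fix the third, and they do not fit together. One symptom equals 0.5 SD only if the SD is 2.0.

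The one-symptom figure is the only difference that the sample-size text gives in the units of the outcome. Because the text says that the two equate, a reader will carry the 90% over to one symptom and may judge a null or borderline result against it. The slip also runs in the favourable direction: it presents the trial as powered for a slightly smaller benefit than the calculation used.

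**Working it through.** **Inputs.** From Sample size: N = 246, power 90%, standardised effect d = 0.5, two-sided 5%, attrition 30%, SD = 2.2, raw difference one symptom. From Randomisation: 1:1. Power below is from the noncentral t distribution for a two-sample t-test, with the normal approximation in brackets where given.

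**Step 1: reproduce 246.**
- Number per arm for d = 0.5 at 90% power: 85.03, rounded up to 86, so 172 analysed.
- Inflation for attrition: 172/(1 − 0.30) = 245.7, rounded up to 246.
- Power at 86 per arm and d = 0.5: 90.3% (normal 90.6%).

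The stated N and power are therefore correct for 0.5 SD, and they come from a calculation without baseline adjustment.

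**Step 2: translate to symptoms.**
- 0.5 × 2.2 = 1.1 symptoms.
- 1/2.2 = 0.4545 SD.

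**Step 3: unadjusted power for exactly one symptom.**
- 86 per arm, d = 0.4545: 84.2% (normal 84.6%). The chance of missing a true difference of exactly one symptom is then about 16% (100 − 84.2), against about 10% for 1.1 symptoms.
- For scale only: 90% unadjusted power at this difference would need 102.7, so 103 per arm or 206 analysed; 206/0.7 = 294.3, so 295 recruited.

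**Step 4: could rounding of the SD explain it?** An SD printed as 2.2 lies between 2.15 and 2.25. Power for one symptom is then 85.8% to 82.6%. It does not reach 90% anywhere in that range.

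**Step 5: effect of the planned baseline adjustment.** If 2.2 is the SD of the follow-up score and r is the baseline to 2-week correlation, the residual SD is 2.2 × √(1 − r²), and the effective standardised effect for one symptom is 1/(2.2 × √(1 − r²)). The article gives no r, so these values are assumptions:

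| Assumed r | Effective d | Power for one symptom, 86 per arm |
|---|---|---|
| 0 | 0.455 | 84.2% |
| 0.3 | 0.476 | 87.4% |
| 0.405 | 0.497 | 90.0% |
| 0.5 | 0.525 | 92.8% |

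The adjusted analysis reaches 90% for one symptom at r of about 0.405, or 0.41 rounded up.

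**The case against.** A reader might infer that the trial has only 84% power where the protocol claims 90%. The article does not support that, for three reasons.

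1. The 90% is attached to the standardised effect ("achieve 90% power to detect an effect size of 0.5 in the primary outcome of cancer symptom recognition"), and for that effect it is correct. No design quantity is wrong: sample size, significance level, attrition and effect size all fit together. The symptom sentence is a gloss on them. This stands.
2. One extra symptom may be 1.1 rounded to a whole count. This is plausible, and the 84% arises only if one is read as exactly 1.0. It does not remove the inconsistency, because the SD is given to one decimal, nothing marks the difference as rounded, and the sentence says that the figures equate.
3. The 84% belongs to an unadjusted comparison, whereas the primary model adjusts for the baseline score. This stands too. Without the correlation, the power of the planned analysis for one symptom is unknown and may be above or below 90%. The unadjusted figure still has some relevance, since the sample size was derived without adjustment and the unadjusted effect will also be reported.

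It is also tempting to say that the SD should have been 2.0. That would make the sentence consistent, but the SD rests on a cited source that is not at hand, and nothing in the article suggests that 2.2 is the wrong figure.

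Finally, the planned 95% confidence interval lets readers judge a null result without the power statement, which limits the harm.

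**Conclusion.** The point holds as a minor inconsistency within the Sample size section. The 246 participants give 90% power for 0.5 SD, which at the stated SD is 1.1 symptoms. One symptom is 0.45 SD, for which an unadjusted comparison of 172 analysed participants has about 84% power. The gap is 0.1 symptom, or about 6 percentage points of unadjusted power (90.3 − 84.2 = 6.1).

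These figures assume exactly 30% attrition, equal arms and an SD of 2.2. The statement about adjusted power also assumes that 2.2 is the SD of the follow-up score and that the correlation is as given in the table. A loss of power in the planned primary analysis is not shown, and there is no ground here to change the sample size.

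**What to change.** Replace the translation sentence, leaving N as it is, with wording such as:

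*With 172 participants analysed (86 per arm), the trial has 90% power for a difference of 0.5 SD, that is 1.1 symptoms at an SD of 2.2, and about 84% power for a difference of one symptom before baseline adjustment. The planned baseline-adjusted analysis would reach 90% power for one symptom if the correlation between the baseline and 2-week scores is about 0.41 or higher; this correlation is an assumption.*

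If the sponsor has an estimate of the correlation, for example from the phase 2 study, it should be stated in place of the threshold. Use the same wording in the statistical analysis plan if it repeats the sample-size text. The cost is one sentence. The power quoted for one symptom becomes less favourable, and no participants or analyses are added.
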